## Abstract

**Background:**

Only 11%-40% of those with a mental disorder in Germany receive treatment. In many cases, face-to-face psychotherapy is not available because of limited resources, such as an insufficient number of therapists in the area. New approaches to improve the German health care system are needed to counter chronification. Web-based interventions have been shown to be effective as stand-alone and add-on treatments to routine practice. Interventions designed for a wide range of mental disorders such as transdiagnostic interventions are needed to make treatment for mental disorders more accessible and thus shorten waiting times and mitigate the chronification of mental health problems. In general, interventions can be differentiated as having either a capitalization (CAP) focus—thus drawing on already existing strengths—or a compensation (COMP) focus—trying to compensate for deficits. Up to now, the effectiveness of transdiagnostic web-based interventions with either a CAP or a COMP focus has not yet been evaluated.

**Objective:**

This study is the first to examine the effectiveness of two transdiagnostic web-based interventions: (1) the activation of resilience and drawing on existing strengths (CAP: Res-Up!) and (2) the improvement of emotion regulation (COMP: REMOTION), compared with care as usual (CAU) in routine outpatient psychotherapy.

**Methods:**

Adults with at least 1 mental health disorder will be recruited at 4 outpatient centers in Germany. Participants will then be randomized equally into 1 of the 2 intervention groups Res-Up! (CAP) and REMOTION (COMP) or into the control group (CAU). Assessments will be made at baseline (T0), at 6 weeks after treatment start (T1), and at 12 weeks after treatment start (T2). A primary outcome will be symptom severity (Brief Symptom Inventory-18). Secondary outcomes will focus on emotion regulation and resilience.

**Results:**

Participant recruitment and data collection started in April 2020 and were ongoing as of July 2022. We expect participants to benefit more from the interventions than from the CAU control on the dimensions of symptom severity, resilience, and emotion regulation. Furthermore, we expect to find possible differences between CAP and COMP. The results of the study are expected in 2023.

**Conclusions:**

This randomized controlled trial will compare CAU with the transdiagnostic web-based interventions Res-Up! and REMOTION, and will thus inform future studies concerning the effectiveness of transdiagnostic web-based interventions in routine outpatient psychotherapy.

**Trial Registration:**

ClinicalTrials.gov NCT04352010; https://clinicaltrials.gov/ct2/show/NCT04352010

**International Registered Report Identifier (IRRID):**

DERR1-10.2196/41413

## Introduction

### Overview

Approximately 1 in 6 people worldwide have met the criteria for a mental disorder in the last 12 months (17.6%); 29.2% have been identified as having experienced a mental disorder at some time in their life [1]. Mental health problems and disorders have a profound impact on individuals affected by symptoms and society as a whole. Still, in Germany, only 11%-40% of patients receive treatment [2], often due to the long waiting times for psychotherapy (20.1 weeks in 2019) [3]. Therefore, the German mental health care system needs innovative intervention concepts, using approaches beyond standard face-to-face therapy and serving a wide range of mental disorders. Transdiagnostic web-based interventions can provide such an approach [4-6].

### Web-Based Interventions

Recent global developments have fast-forwarded digitalization, and thus the use of web-based tools to support mental health care has rapidly increased all over the world. Research on web-based interventions in psychotherapy supports the effectiveness of different intervention programs for a variety of mental disorders [5,7,8]. With limited access to psychotherapy, web-based interventions are an economical, flexible, and practical alternative or addition to conventional treatment [5]. Particularly when face-to-face psychotherapy is not available because of limited resources (like insufficient availability of therapists), web-based interventions can help to avoid long waiting times for treatment and thus mitigate the chronification of mental health problems [4].

Among web-based interventions, stand-alone web-based programs can be differentiated from blended treatment (BT)—the combination of face-to-face psychotherapy and a web-based intervention [9]. Although BT can take on many different forms [10], a differentiation can be made between integrated blends (eg, conceptual coordination between web-based intervention elements and face-to-face psychotherapy sessions via a specified protocol) and add-on blends (eg, a web-based intervention provided in parallel before or after face-to-face psychotherapy without conceptual coordination or integration between the two). BT, where a web-based intervention was provided as an add-on to face-to-face psychotherapy, has been shown to be more effective than psychotherapy alone [11]. A transdiagnostic approach might be particularly relevant for add-on conceptualizations as coordination with a potential face-to-face therapy focusing on a specific disorder is less relevant.

Although even unguided web-based interventions (without any contact between the patient and the provider of the intervention) seem to be effective, therapist-supported web-based interventions are most likely more effective than self-guided treatments [5,12,13]. Although the exact mechanism behind the benefit of guidance remains unclear, this may be due to higher adherence and lower dropout rates resulting from the positive effect of the accompanying support on motivation and on engagement with the intervention [5,11].

### Capitalization or Compensation: Basic Orientations in Psychotherapy

Overall, a differentiation has been made in psychotherapy research between capitalization (CAP)–oriented versus compensation (COMP)–oriented *interventions*. CAPs aim to draw on the person’s already existing strengths (in a wide sense: action repertoire, resilience strategies, and external and internal resources), and COMPs identify dysfunctional maintenance factors of psychopathology and teach (respectively train) the person to use new strategies or build new behavior against relative deficits [14-18]. In an early study, Wingate et al [18] compared the outcomes of compensation versus capitalization in the treatment of suicidality in young adults, finding results favoring COMPs, whereas other studies find results favoring CAPs [14,17]. According to the current sparse research, there is no agreement on which of these 2 strategies should be pursued in psychotherapy [14,17,19-22].

Certain interventions in psychotherapy are inherently more focused on capitalization (eg, focusing on action repertoire, resilience strategies, and external and internal resources) or on compensation (eg, focusing on the building of new strategies for deficit compensation). Although outcome differences between CAPs and COMPs in face-to-face psychotherapy seem to be small [14], there are no studies comparing the 2 approaches for web-based therapy. Web-based therapy involves less therapeutic guidance and thus relies more strongly on the person’s self-management capacities. Thus, the possible effects of therapists’ support in face-to-face therapy compensating deficits in both CAP and COMP cease in a web setting. Thus, this randomized controlled trial explores, for the first time, the effect of 2 transdiagnostic web-based interventions inherently capitalization or compensation oriented: activation of resilience (CAP) (respectively improvement of emotion regulation [COMP]) compared with a care-as-usual (CAU) group.

As discussed above, capitalization and compensation can be conceptualized as features of interventions. Another possible conceptualization is via the interaction of intervention focus with patient variables. If particularly patients with a high level of adaptive emotion-regulation strategies profit from an intervention focusing on the improvement of emotion-regulation strategies, this would point toward a capitalization change process. If patients with a low level of adaptive emotion-regulation strategies profit particularly from an intervention focusing on the improvement of emotion-regulation strategies, this points to a compensation change process. Thus, in this trial, differential effects of patients’ initial resilience (respectively emotion-regulation competencies) on the outcome of a resilience and emotion-regulation intervention will also be explored.

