### Emotion Regulation

Emotion regulation refers to the way individuals attempt to influence emotions and includes the upregulation and downregulation of positive and negative emotions in accordance with regulatory goals [33]. Emotion regulation and specifically the fostering of flexible use of different emotion-regulation strategies are important topics in the treatment of mental health disorders and more specifically in psychotherapy research. This is made evident by the large number of publications that focus on the topic of emotion regulation [34-37]. Interestingly, emotion regulation has been discussed as a transdiagnostic factor related to psychopathology and the treatment of mental health disorders [34,38-40]. More recently, several mental health interventions that address or target emotion regulation have been developed as web- or mobile-based programs. For example, Böhme and Berking [41] describe the application of an emotion regulation app based on Affect Regulation Training.

By using the extended process model of emotion regulation as a theoretical framework to structure an emotion-regulation intervention [42], Bielinski et al [43] developed REMOTION. The web-based program aims to reduce the symptom severity of patients with a range of different diagnoses while improving their emotion regulation [43]. REMOTION is currently being examined as a blended intervention in an outpatient psychotherapy setting in a pilot randomized controlled trial [43]. It is also currently being examined as an add-on to acute inpatient psychiatric care in another pilot randomized controlled trial (ClinicalTrials.gov NCT04990674). Results for both trials are expected in 2023.

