### Aims

Web-based interventions have been efficient and helpful in considering different mental disorders and in self-selected samples in many controlled studies [7]. Nevertheless, little is known about the efficacy of web-based interventions in routine psychotherapeutic practice and their usefulness as an add-on to conventional psychotherapy (BT).

The *first goal* of this study is to assess the effectiveness of 2 web-based interventions (Res-Up! and REMOTION) in an outpatient psychotherapeutic routine setting in comparison with CAU.

The *second goal* of this study is to explore, in a web-based therapy context, the implementation of interventions with either a CAP or COMP focus by using 2 transdiagnostic web-based intervention programs, centered either on activating resilience (CAP; “Res-Up!”) or on emotion regulation (COMP; “REMOTION”).

Further subanalyses considering differences in patients’ benefits depending on their diagnoses will be conducted. In addition, the differential effects of initial resilience and emotion-regulation competencies on the effectiveness of Res-Up! and REMOTION will be explored. To accomplish this, the initial status of resilience and emotion-regulation competencies will be assessed and related to intervention effects in the intervention groups.

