#### Primary Outcome Measure

The primary outcome measure in this study is general symptom severity measured with the Brief Symptom Inventory—a short form (BSI-18; German version) [55] of the Symptom-Checklist-90-Revised (SCL-90R) [65]. The BSI-18 has 18 items and is a frequently used questionnaire to measure general symptom severity (Cronbach α=.85-.89) with good psychometric properties [56], comparable to those of the SCL-90R [65].

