## Discussion

### Principal Findings

This study aims to compare a CAU control with 2 transdiagnostic web-based intervention programs, focusing either on resilience (as an example of capitalization strategies) or on emotion regulation (as an example of compensation strategies).

In accordance with previous research [11], we hypothesize that both interventions will be more efficacious than no additional treatment (CAU). According to Fuhr et al [12], web-based interventions that focus on individual parts of psychotherapy—preferably in a blended approach—might be more effective than all elements of a disorder-specific therapy when implemented in a routine setting. Because of the dearth of studies comparing CAP versus COMP interventions directly, no directed hypothesis can be formulated in this context. While the primary outcome targets symptom severity, secondary outcomes assess resilience and emotion regulation as the specific target areas of the individual interventions.

The study will be conducted in Germany in 4 outpatient centers in a clinical sample of approximately 300 participants, 100 in each of the 3 study arms. Matching the transdiagnostic approach of the interventions, participants in the sample will have a variety of different mental disorders and varying symptom severity.

Results from this study will be valuable for practitioners, patients, and mental health services in all fields, due to the transdiagnostic approach. Furthermore, it will contribute to the knowledge and efficacy of evidence-based web-based intervention programs and possibilities of implementation in outpatient routine care. In particular, it will create new knowledge for web-based interventions focusing on resilience and emotion regulation and thus shine light on possible differences of capitalization- and compensation-oriented interventions in web settings.

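### A capitalization or compensation label read from the baseline-skill gradient within one programme can reflect regression to the mean or a general severity effect, so it should rest on the difference in skill slopes between the two programmes

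*Protocol article*

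**What the plan says.** The last paragraph of the Introduction section on capitalization and compensation offers a second way to define the two processes: through the way an intervention's focus interacts with characteristics of the patient. It then gives a reading rule for the emotion-regulation programme. If patients who already have many adaptive strategies profit most, "this would point toward a capitalization change process". If patients with few strategies profit most, "this points to a compensation change process". The paragraph closes by extending the idea to both programmes: "differential effects of patients’ initial resilience (respectively emotion-regulation competencies) on the outcome of a resilience and emotion-regulation intervention will also be explored".

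The Aims section repeats the intention ("the differential effects of initial resilience and emotion-regulation competencies on the effectiveness of Res-Up! and REMOTION will be explored") and says where the gradient will be looked for: baseline status will be "related to intervention effects in the intervention groups". The Results section says the same. None of these places names a contrast with CAU, a comparison of the gradient between the two programmes, or an allowance for baseline severity.

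Three other statements bear on the point. In the section on emotion regulation, "emotion regulation has been discussed as a transdiagnostic factor related to psychopathology". The outcome is symptom burden: "The primary outcome measure in this study is general symptom severity measured with the Brief Symptom Inventory". The Discussion expects that "participants in the sample will have a variety of different mental disorders and varying symptom severity".

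**The concern.** The rule turns a gradient seen in one programme into a statement about mechanism. If patients with low skill also tend to have more symptoms, that gradient has at least two other possible sources. One is regression to the mean: patients with high baseline scores fall further on the BSI-18 whatever they receive. The other is a benefit that is larger in more severe patients and has nothing to do with the skill that the programme trains. Both push the gradient towards greater gain at low skill, in both programmes. Two programmes that work alike could then both appear to be compensation, and a real capitalization gradient could be masked. The article says that no study has compared the two approaches in web-based therapy, so the labels are likely to be taken up by others.

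**Working it through.** The plan attaches no figure to this analysis, so there is none to reproduce. The question is how often the rule would return a compensation label when no skill-specific process exists.

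**Inputs from the article.** 100 randomized per arm and about 25% dropout (Sample Size Calculation), so 100 × (1 - 0.25) = 75 completers per arm. Outcome: BSI-18.

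**Assumptions, because the article gives no values.** Scores are standardised to SD 1. Skill-severity correlation r is -0.3 to -0.6. Baseline-outcome correlation s of the BSI-18 is 0.5, with 0.6 as an alternative. Both programmes have the same effect, which rises by λ SD per SD of baseline BSI-18 (λ = 0 means the same effect for everyone). Skill has no effect of its own. Profit is taken as improvement on the BSI-18.

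**Expected slope of improvement on baseline skill** (negative reads as compensation):

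- within one programme: r(1 - s + λ)
- arm × skill against CAU: rλ
- arm × skill against CAU, with arm × baseline BSI-18 added: 0
- difference between the two programmes: 0

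**Within a programme, λ = 0, s = 0.5.** The variance of improvement is (1 - 0.5)² + (1 - 0.5²) = 1.00, so the SE of the slope is √[(1 - slope²)/75].

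- r = -0.3: slope -0.15, SE √(0.9775/75) = 0.114, ratio 1.31. Chance of a significant compensation slope in one programme: Φ(1.31 - 1.96) = 0.26. The arms are independent, so for both: 0.26² ≈ 7%.
- r = -0.5: slope -0.25, SE √(0.9375/75) = 0.112, ratio 2.24. One programme: Φ(0.28) = 0.61. Both: 0.61² ≈ 37%; simulation gives 34% to 36%.

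With s = 0.6 the slopes are -0.12 and -0.20, and simulation labels both programmes in 4% and 24% of trials. With r = 0 there is no artefact.

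**Same setting (r = -0.5, λ = 0, s = 0.5), other contrasts.** Against CAU, both programmes are labelled in 0.5% of trials. The between-programme slope difference is significant in 5%, its nominal rate.

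**Benefit growing with severity, against CAU.** The expected slope is -0.5 × 0.2 = -0.10, or -0.6 × 0.3 = -0.18. One programme is significantly labelled in about 10% and 23% of trials (nominal 2.5%), and both in about 3% to 12%. Baseline BSI-18 as a main effect alone does not remove this slope. Adding arm × baseline BSI-18 does: the false-label rate for one programme is then 2.1% to 2.6%. The between-programme difference keeps about 4% to 6% false positives without that term.

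**The case against.** The strongest case against the point has four parts.

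- The rule stands in an Introduction, is worded cautiously and concerns an exploratory analysis. A journal article need not list the covariates of such a model. This is fair, and the missing covariate list is not the point. The point is that the stated rule does not support the label it gives.
- The phrase on effects in the intervention groups can be read as effects relative to CAU. It can, and regression to the mean then cancels. But neither Aims nor Results says so, and the within-arm reading is at least as natural.
- The paragraph introduces the idea as an interaction with intervention focus, which already suggests comparing the two programmes. This stands and supports the remedy: the between-programme contrast follows from the article's own definition, whereas the two conditional sentences look at one programme only.
- Severity may partly result from low skill, so adjusting for arm × severity could absorb a real compensation process. Res-Up! also improved emotional competence in preliminary results (d = 0.51), so a process shared by both programmes is possible. This stands. It is why the arm × severity term belongs in a sensitivity analysis, and why a shared gradient should be called not specific to intervention focus rather than proof of a severity effect.

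A reader might go further and infer that both programmes would be labelled compensation even against CAU. The documents do not support that. With a constant effect the arm × skill slope against CAU is zero. A bias there needs a benefit that grows with severity, which the article nowhere states, and even then both programmes are labelled in only a small share of trials. Nor is this the trial's second goal. That goal is to explore interventions with either focus; the baseline-skill question is an additional analysis.

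**Conclusion.** The concern holds in limited form. Read within a programme, the skill gradient cannot separate a skill-specific process from regression to the mean or a general severity effect, and the error leans towards compensation. With a constant effect and 75 per arm, two identical programmes would both be significantly labelled in about 7% of trials at r = -0.3 and 36% at r = -0.5 (4% and 24% if the baseline-outcome correlation is 0.6). Against CAU this part disappears. What remains depends on an assumed severity gradient of 0.2 to 0.3 SD per SD, and amounts to about 10% to 23% for one programme and 3% to 12% for both.

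All these figures rest on a negative skill-severity correlation that the article supports only in words, and on profit meaning BSI-18 improvement. The rule is spelled out for emotion regulation; its use for resilience is implied. The primary comparison with CAU is untouched.

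**What to change.** Revise the last paragraph of the capitalization and compensation section, and the matching sentences in Aims and Results, to say that:

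1. arm × baseline skill will be estimated in the three-arm model with CAU as reference, adjusted for baseline BSI-18;
2. a capitalization or compensation label will rest on the difference in skill slopes between Res-Up! and REMOTION, reported with a 95% CI;
3. a gradient common to both programmes will be described as not specific to intervention focus;
4. arm × baseline BSI-18 will be added as a sensitivity analysis, with a note that severity may partly follow from low skill.

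No new data are needed, because Table 1 shows the BSI-18 and the resilience and emotion-regulation scales collected at baseline. The cost is precision: a difference between two independent slopes has an SE about √2 times that of one slope, so intervals widen and fewer process claims will be possible. That is acceptable for an exploratory analysis.

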### Resilience

Resilience as psychological resistance to adversity was originally conceptualized in the context of developmental psychology [23,24]. Today, resilience and resources are often discussed in the field of positive psychology [25], which focuses on factors that make and keep people healthy rather than ill. Although most research on resilience and resources has a compensation focus, aiming to create new resources and building up new strengths [26], the personal model of resilience (PMR) is a CAP intervention that was developed by Padesky and Mooney [27] from a cognitive perspective.

The PMR focuses on individuals’ pre-existing resources and resilient strategies to increase awareness and implementation of these strengths. The basic assumptions of the PMR are as follows: every person is resilient and has resilience strategies that are already part of their action repertoire and have the potential to also be used in challenging situations. The model is based on evidence-based standards for cognitive behavioral therapy [28].

The model was evaluated in a pilot study with students [29], a randomized study with a waiting control group [30], and in a web version with active plus waiting control groups (web-based intervention program vs face-to-face vs ABC [activating events, belief systems, emotional and behavioral consequences] model vs waiting control group) [31]. Medium effect sizes for the face-to-face model and small effect sizes for the web version were observed. Based on the feedback of participants, the web version was redesigned and is being re-evaluated [32]. The redesigned version of the program (Res-Up!: Resilience program of the University of Witten/Herdecke) showed medium effect sizes in preliminary results for resilience (*d*=0.51-0.55) and emotional competence (*d*=0.51), greater effect sizes for self-compassion (*d*=0.70), and small effect sizes for self-esteem (*d*=0.41) [32].

